### Ancillary for post-trial care

With regard to the nature of mobile-based patient education, participants are unlikely to be harmed. In the event that a risk of injury is discovered, the principal investigator will intervene to reduce the risk of harm. If any harm is discovered, the research team will compensate the participants appropriately if necessary.

### Outcomes

#### Primary outcome measures

The primary endpoint is the percentage of fasting blood glucose, which is defined as the percentage of blood glucose levels within a normal range [17]. Glucose monitoring data is collected twice weekly after enrollment [time frame: from randomization (day 0) to V5 (week 12) for a total of 3 months of treatment]. The selected examination days shall be at least 2 days apart. Each examination day should contain the following self-monitoring data.

**Table Tabc:** 

	Type	Measuring time	Normal range
1	Fasting blood glucose	Before breakfast	3.3–5.3 mmol/L
2	1-h postprandial blood glucose	After breakfast	3.3–7.8 mmol/L
3	2-h postprandial blood glucose	After breakfast	3.3–6.7 mmol/L
4	1-h postprandial blood glucose	After lunch	3.3–7.8 mmol/L
5	2-h postprandial blood glucose	After lunch	3.3–6.7 mmol/L
6	1-h postprandial blood glucose	After dinner	3.3–7.8 mmol/L
7	2-h postprandial blood glucose	After dinner	3.3–6.7 mmol/L

#### Secondary outcome measures

1) The percentage of blood glucose levels collected within the normal range on each selected examination day.2) Loss of self-monitoring rate.3) HbA1c.4) Mean score of Diagnostic and Statistical Manual of Mental Disorders (DSM-5) assessment. DSM–5 is developed as a standard classification system for mental disorders. It provides a guideline of structured clinical interviews utilized to diagnose depression [18]5) Mean score of General Self-Efficacy Scale (GSE). The GSE is a psychometric scale that measures the confidence in one’s capacity to deal with a wide range of life’s issues. The test consists of ten items that describe attitudes toward barriers and are assessed on a scale of 0 (least optimal) to 4 (very optimal). A version in Chinese translation has been approved [19]6) Any insulin dose prescribed.7) Case number of low-birth-weight neonates. Low birth weight is defined as the first weight recorded after the birth of less than 2500 g (up to and including 2499 g) [20]8) Case number of neonatal macrosomia. Neonatal macrosomia is defined as the first weight recorded after the birth of more than 4000 g (more than and including 4000 g) [21].9) Hypoglycemic events in neonates (blood glucose < 2.2 µmol/L).10) Other fetal adverse events.11) Case number of GDM comorbidity developed during the intervention period.12) Case number of cesarean delivery.13) Total expenditures for delivery.

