**Methods:**

This trial is designed as a prospective randomized controlled trial, which enrolled the patients diagnosed with GDM in First People’s Hospital of Kunshan affiliated with Jiangsu University from September 2021 to March 2023 with a 3-month follow-up. The specific randomization method was established and implemented through the central randomization system of EDC clinical trials. The percentage of all blood glucose levels collected within the normal range between the two groups at baseline, during the intervention period, and postpartum infant and maternal outcomes will be measured. Summary statistics for continuous variables will include the number of subjects, mean, median, SD, or the standard error, minimum, and maximum. The chi-square test, *t* test, and paired-sample *t* test were used for statistical analysis of differences between groups.

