### Statistical methods

#### Statistical methods for primary and secondary outcomes

Categorical variables will be expressed in numerical values with their respective percentages and compared using the chi-squared test at baseline. Continuous variables will be expressed as mean ± SD and compared using the *t*-test. The significance of primary and secondary endpoints will be evaluated with the paired-samples *t*-test. A *p*-value < 0.05 indicates statistical significance. All data will be analyzed with the SPSS.

All patients who have received CBT for at least 4 weeks will be included in the full analysis set (FAS). Depending on the time investigated, the per-protocol (PP) analysis set will be made up of patients who complete the 6-month follow-up examinations. The FAS will be used as the basis for the primary analysis. If there is a discrepancy of greater than 10% between the FAS and PP samples, the analysis will be repeated for the PP analysis set. The safety population will include patients in the FAS. Unless otherwise noted, all analysis will be done in both the FAS and PP analysis sets. No additional analysis will be conducted.

There will be no replacement or imputation of missing values. All analysis will be based solely on observed cases. Patients who loss to follow-up will be considered to have dropped out of therapy. Only the PP patients will be used in a sensitivity analysis to test the impact of this assumption.

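### Secondary outcome 1 is defined per examination day but is given a t-test, with no per-woman summary or repeated-measures method fixed, so its false-positive rate depends on an unstated choice

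*Protocol article*

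**What the plan says.** The Trial design section randomises individual patients 1:1, so the woman is the unit of allocation. Item 1 under Secondary outcome measures is "The percentage of blood glucose levels collected within the normal range on each selected examination day", which is a day-level quantity.

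The schedule is under Primary outcome measures: "Glucose monitoring data is collected twice weekly after enrollment", over a window running "from randomization (day 0) to V5 (week 12) for a total of 3 months of treatment". On spacing and content it adds "The selected examination days shall be at least 2 days apart" and "Each examination day should contain the following self-monitoring data". The table that follows lists seven readings, one fasting and six after meals.

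The section Statistical methods for primary and secondary outcomes states: "The significance of primary and secondary endpoints will be evaluated with the paired-samples" t-test, with p below 0.05 as the threshold. Just before that it says: "Continuous variables will be expressed as mean ± SD and compared using the" t-test. The Abstract gives the same short list: "The chi-square test, *t* test, and paired-sample" t-test. The statistical methods also restrict analysis to observed cases without imputation, and rule out further analyses. No method for repeated or clustered values is named, and no step reduces a woman's daily values to one number.

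**The concern.** A two-sample t-test assumes independent observations, one per randomised unit. A paired t-test assumes independent pairs. A woman's percentages on different days are likely to be correlated, because they share her diet, physiology and adherence. An outcome with up to 24 such values per woman does not fit either test until someone decides how to reduce or model the values.

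Taken literally, a day-level outcome with a t-test points to one test per day, or to one test on all woman-days as if they were independent. The first makes a chance result on some day likely. The second gives a standard error that is too small. In either case a nominally significant result for item 1 could arise with no effect of the app.

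This is separate from whether the test should be paired. The two arms contain different women, so a paired test does not compare them. Replacing it with a two-sample test would still leave several values per woman.

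**Working it through.** **Inputs from the protocol article.** Two examination days a week for 12 weeks: 2 × 12 = 24 planned days per woman. Evaluable sample: 80 women per arm (Sample size section). Threshold: p < 0.05. The statistical methods do not state sidedness, so two-sided is assumed here; the sample size section uses one-sided 0.05.

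**The plan's own figure.** The article states no false-positive rate for this outcome, so there is none to reproduce. The step from 80 to 100 per arm does reproduce, 80 / (1 − 0.2) = 100, but has no bearing on this point.

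**Assumptions.** The article gives no within-woman correlation, so a range is used. There is no true effect, every woman has all 24 days, correlation is equal between any two days, and data are normal. Simulations used 80 women per arm and 3,000 runs per correlation.

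**Route A: one mean per woman, two-sample t-test.** The simulated false-positive rate was 4.6% to 5.5% at every correlation from 0 to 0.7. Simulation error near 5% is about √(0.05 × 0.95 / 3000) = 0.4 points, so this agrees with the nominal 5%.

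**Route B: all woman-days pooled as independent.** The design effect is DE = 1 + (24 − 1) × ICC, and the true rate is 2 × [1 − Φ(1.96 / √DE)]. At ICC 0.1, DE = 1 + 23 × 0.1 = 3.3 and the rate is 2 × [1 − Φ(1.96 / 1.817)] = 28%. Simulation agrees (28.9% at 0.1, 64.2% at 0.7).

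**Route C: a separate test on each of 24 days.** With independent days, the chance of at least one p < 0.05 is 1 − 0.95^24 = 70.8%. Correlation lowers it (simulated values in the table). These are familywise rates; each single daily test stays at 5%.

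**Route D: paired t-test on the two arms' 24 daily means.** This is one way to apply a paired test between arms. The true variance of the mean difference exceeds the estimated variance by a factor 1 + 24ρ / (1 − ρ), which is 3.67 at ρ = 0.1 and 25 at ρ = 0.5. On 23 degrees of freedom this gives about 29% and 68%, close to the simulation.

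| Assumed correlation | 0.02 | 0.1 | 0.3 | 0.5 | 0.7 |
|---|---|---|---|---|---|
| Design effect (B) | 1.46 | 3.3 | 7.9 | 12.5 | 17.1 |
| A: one mean per woman | not run | 5.5% | 5.2% | 4.6% | 5.1% |
| B: pooled days | 10.5% | 28% | 49% | 58% | 64% |
| C: any of 24 tests | not run | 68% | 61% | 47% | 32% |
| D: paired daily arm means | not run | 30% | 55% | 69% | 79% |

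**Fewer days.** Observed-case analysis means some women will have fewer than 24 days. If every woman had half, 24 / 2 = 12, Route B would have DE = 1 + 11 × 0.1 = 2.1 at ICC 0.1, and a rate of 2 × [1 − Φ(1.96 / 1.449)], about 18%. At ICC 0.7, DE = 8.7 and the rate is about 51%. The inflation shrinks but remains.

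**The case against.** The strongest reply is that the article never says days will be pooled or tested one by one. Averaging each woman's daily percentages and applying the named t-test is ordinary practice, nothing in the text forbids it, and it holds 5%. A condensed article may also leave such a step to an analysis plan that is not shown. The sentence ruling out further analyses directly follows the one on analysis sets. It may exclude only extra analyses of that kind, and it does not bar computing a per-woman mean.

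Much of this stands. A reader might infer that the p-value for this outcome must have a false-positive rate far above 5%. The documents do not support that: they do not choose Routes B, C or D, Route A is open, and the ICC is an assumption. At an ICC of 0.02 even pooling gives only 10.5%. The Route C figures are familywise, and the article claims no familywise control for secondary outcomes.

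The reply does not dispose of the point. The article is not silent on method: it defines the outcome by day and names a specific test for all secondary endpoints, and the two do not fit. Averaging is nowhere stated, and it sets aside the day-level definition. If the primary endpoint is read as all readings in range, the per-woman average nearly duplicates it. If the primary is fasting glucose only, the average is a distinct outcome but still has to be specified.

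**Conclusion.** The point holds in conditional form. Item 1 is a day-level outcome with up to 24 correlated values per woman. The test assigned to it takes one value or one pair per woman, and neither a summary nor a repeated-measures method is fixed. The false-positive rate is about 5% with per-woman averaging and a two-sample test, about 28% to 64% with pooled days at an assumed ICC of 0.1 to 0.7, and about 68% to 32% familywise with 24 daily tests over the same range of correlation. All but the first rest on assumed correlations, complete monitoring and a two-sided 5% threshold.

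The consequence is limited to one of 13 listed secondary outcomes. A reader might extend it to the primary endpoint, which draws on the same monitoring schedule. The documents do not support that here, because the primary is not worded as a value for each examination day.

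**What to change.** In Statistical methods for primary and secondary outcomes, give secondary outcome 1 its own sentence. Analyse the day-level percentage in one model clustered on woman: a linear mixed model with arm, study week, arm-by-week and a random effect for woman, or a GEE clustered on woman with robust standard errors. Choose one in advance, since the two differ in what they assume about missing days and the plan uses observed cases only. Test one pre-stated contrast, the arm difference averaged over weeks 1 to 12. Show weekly differences with confidence intervals as description, without separate significance claims.

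At minimum, define the outcome as the mean of each woman's daily percentages and compare arms with a two-sample t-test. This holds the 5% level but gives up the time course.

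The cost is one sentence and a standard procedure in the SPSS software already named. No new data or participants are needed. The interval will be wider than a pooled analysis would show, because it reflects the number of women rather than the number of woman-days.

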### Objectives

Aim 1: To determine the efficacy in treating hyperglycemia of mobile-based CBT interventions in GDM patients, compared with conventional face-to-face interventions.Hypothesis 1a (primary study hypothesis): a significant difference in the percentage of blood glucose levels within a normal range is expected between the two groups. The normal range is defined as fasting blood glucose.

Aim 2: To determine the efficacy of mobile-based CBT interventions in infants and maternal outcomes, compared with conventional face-to-face interventions.Hypothesis 2a: a significant difference in the variables evaluating infants and participants outcomes, including low-birth-weight neonates, neonatal macrosomia, events of hypoglycemic events in infants, and cesarean delivery, is expected between two groups.

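### Secondary outcome 9 sets the neonatal hypoglycaemia threshold in µmol/L while every other glucose limit is in mmol/L, so read literally no neonate could realistically qualify (minor, one secondary outcome)

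*Protocol article*

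**What the plan says.** In the protocol article, the list under Secondary outcome measures has 13 items. Item 9 is the only place where neonatal hypoglycaemia is given a case definition: "Hypoglycemic events in neonates (blood glucose < 2.2 µmol/L". No other section restates or corrects the threshold.

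The table under Primary outcome measures gives seven maternal glucose ranges: one fasting, and 1-hour and 2-hour values after each of three meals. All seven are in mmol/L. The unit µmol/L appears nowhere else in the article.

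The outcome also belongs to a stated hypothesis. Under Objectives, Hypothesis 2a lists "events of hypoglycemic events in infants" with low birth weight, macrosomia and cesarean delivery as outcomes on which the arms are expected to differ.

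**The concern.** A threshold in µmol/L beside a table in mmol/L is a conflict of units by a factor of 1,000. It sits in an operative definition. The two preceding items, low birth weight and macrosomia, are also defined by numeric cut-offs, and a data manager would naturally program the eCRF and derivation from this list.

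What is at stake is the event count for one secondary outcome. With a threshold that no infant can meet, the count is zero in each arm whatever the true rate. The comparison planned under Hypothesis 2a would be empty, and the result could pass for a genuine finding of no events. Anyone reusing the published definition, in a later trial or a review, would inherit the same problem.

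**Working it through.** The threshold is a definition and is not derived from other figures in the plan, so there is no stated result to reproduce. The check is a unit conversion.

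**Inputs**
- Neonatal threshold as stated: 2.2 µmol/L (Secondary outcome measures, item 9).
- Unit used for all other glucose limits: mmol/L, stated to one decimal (table under Primary outcome measures).
- Conversion: 1 mmol/L = 1,000 µmol/L.

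**Step 1. Put the threshold on the protocol's scale.**
2.2 µmol/L ÷ 1,000 = 0.0022 mmol/L.

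**Step 2. Size of the discrepancy.**
The same number in mmol/L, divided by the threshold as written: 2.2 / 0.0022 = 1,000.

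**Step 3. Could a recorded value qualify?**
Assume that neonatal values are recorded to one decimal in mmol/L, as in the table. The smallest non-zero reading is then 0.1 mmol/L, and 0.1 / 0.0022 ≈ 45 times the threshold. With two decimals the smallest non-zero reading is 0.01 mmol/L, and 0.01 / 0.0022 ≈ 4.5 times the threshold. At either precision only a reading of zero would count as an event.

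**Step 4. Consequence under each way of building the outcome.**
- If the unit is applied (values in mmol/L are converted before comparison, or the threshold is programmed as 0.0022 mmol/L), the expected count is zero in both arms and the arms cannot be compared.
- If the reading is entered in mmol/L and the bare number is compared with 2.2, the printed unit has no effect on the count. The error then stays on the page.

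The article does not show which of these applies.

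**The case against.** The strongest reply is that this is an evident slip in one symbol. Clinical staff who see 2.2 near a table in mmol/L would read it in mmol/L, and nothing shows that the µmol/L figure was ever programmed. That is fair, and it limits the point to the definition as written. It does not remove the point, because the eCRF, edit checks and derivation are not shown and no reader can confirm that the slip went no further. The safeguard under Data management, where queried values are checked against original records, would not necessarily help: a correctly transcribed reading passes that check and can still be misclassified by a wrong threshold.

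A misreproduced symbol cannot be wholly excluded either. However, the table shows mmol/L all seven times, so it is an unlikely explanation.

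A reader might infer that the trial will report zero events, or that a neonatal safety signal will be lost. The documents do not support either. The first holds only if the text was built in literally. As to the second, item 10 separately collects further fetal adverse events, and the section on adverse event reporting covers the type and frequency of any adverse event. Neither replaces the comparison under item 9, and item 10 may be read as excluding hypoglycaemia, but both leave a route for an event that clinicians recognise.

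A reader might also set the threshold against the lower limit of the maternal ranges. Those ranges show the unit and scale in use. They are not a neonatal cut-off, so the relevant discrepancy is the factor of 1,000 in the unit.

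It is also true that the scope is narrow: this is one of 13 secondary outcomes, and Hypothesis 2a presents its four named outcomes as examples, not a closed list.

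**Conclusion.** The point holds as a unit error in an outcome definition: wrong as written, and minor. The stated threshold is 0.0022 mmol/L, a thousandfold below the same number on the scale that the protocol uses everywhere else, and no neonate could realistically meet it. Loss of the comparison is conditional on the text having been carried with its unit into the eCRF, an edit check or the derivation. In that case one of the four outcomes named in Hypothesis 2a has no events in either arm. The other three, the primary endpoint and the sample size are untouched.

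The size of the discrepancy rests on the conversion alone. That no reading could qualify rests on values being recorded to one or two decimals in mmol/L, which is an assumption. That µmol/L is a slip for mmol/L is the likeliest reading, but the article does not state the intended threshold, and this review does not supply one.

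The error gives no ground for asking for a different analysis of this outcome. How events per infant are counted and compared is a separate question that the unit does not raise.

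**What to change.** The sponsor should:

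1. Reconcile the unit in item 9 of the secondary outcome measures with the mmol/L scale of the glucose table, and confirm the intended threshold.
2. Check that the eCRF field, any edit check and the derivation of the outcome carry that unit and threshold.
3. If the µmol/L figure was programmed, derive the outcome again from the recorded glucose values.

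The first step is a one-line correction. The second is a short check of the data system. The third is needed only if the second finds the error, and requires that the glucose readings themselves were kept and not only an event flag. Nothing else in the design changes.

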### Participant timeline

The participant timeline is shown in Fig. 2.

**Fig. 2 Fig2:**
[figure not shown]
Participant timeline

### Sample size

Considering the primary outcome variable as the difference in the percentage of blood glucose within normal range between two groups, an absolute difference of 10% in the percentage of blood glucose within normal range is expected. Power was set at 0.8, the one-sided significance level at 0.05, and the confidence interval (CI) at 95%. Eighty subjects per group were calculated according to a 1:1 ratio of random grouping. A total sample size 100 was needed in each group that to account for an additional 20% in attrition size.

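### The one-sided 0.05 sizing does not fit the 95% CI, the non-directional hypothesis and the unqualified p < 0.05; if the final test is two-sided, power at 80 per group is about 70%

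*Protocol article*

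**What the plan says.** Three sections of the protocol article bear on the success threshold for the primary endpoint.

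- **Sample size.** The planned effect is stated as follows: "an absolute difference of 10% in the percentage of blood glucose within normal range is expected". The error rates are: "Power was set at 0.8, the one-sided significance level at 0.05, and the confidence interval (CI) at 95" per cent. The result is: "Eighty subjects per group were calculated according to a 1:1 ratio of random grouping", raised to 100 per group for 20% attrition.
- **Objectives, primary hypothesis.** What is expected is "a significant difference in the percentage of blood glucose levels within a normal range is expected between the two groups". No direction is given.
- **Statistical methods for primary and secondary outcomes.** The decision rule is that a p-value "< 0.05 indicates statistical significance". Sidedness is not mentioned.

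The Sample size section is the only place where a one-sided level appears, and nowhere does the article describe the test or the interval as two-sided. No SD or control-group rate accompanies the 10-point difference.

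**The concern.** By the usual correspondence, a one-sided 5% test goes with a two-sided 90% CI, and a two-sided 95% CI goes with a one-sided 2.5% test. The Sample size sentence takes one element from each pair. The two sections that govern the final claim, a difference in either direction and a plain p < 0.05, read most naturally as a two-sided 5% test. The one-sided level therefore appears only where it lowers the required number.

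Two things are at stake. If the test is two-sided, a null result will be read against 80% power that the design does not have. If it is one-sided, a superiority claim carries twice the false-positive risk that a reader of a two-sided 95% CI would assume. A one-sided p between 0.025 and 0.05 would succeed under the Sample size section and fail against a two-sided 95% CI. The trial is open-label and its primary endpoint comes from self-monitored glucose, so this choice should be settled before results are seen.

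**Working it through.** **Inputs from the Sample size section:** one-sided alpha 0.05, power 0.80, difference 10 points, 80 evaluable per group, 1:1 allocation, 20% attrition. Normal quantiles: 1.645 (one-sided 0.05), 1.960 (two-sided 0.05), 0.842 (power 0.80). Sums below use unrounded quantiles.

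**1. The plan's own figures.** Attrition reproduces: 80 / (1 − 0.20) = 100. The 80 cannot be rebuilt from the stated inputs, because the article gives no SD or control rate. It can only be solved backwards: SD = 10 × √(80/2) / (1.645 + 0.842) = 25.4 points. This is a derived value, not the sponsor's, and step 2 does not need it.

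**2. Power if the final test is two-sided.** If 80 per group gives 80% power at one-sided 0.05, the planned difference divided by its standard error is

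1.645 + 0.842 = 2.486.

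The SD is absorbed in this ratio and drops out. Tested two-sided at 0.05:

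- 80 evaluable per group: Φ(2.486 − 1.960) = Φ(0.526) = 0.70
- 100 evaluable per group: 2.486 × √(100/80) = 2.780, and Φ(2.780 − 1.960) = Φ(0.820) = 0.79

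The chance of missing a true 10-point difference at 80 per group rises from 20% to about 30%.

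**3. Cross-checks.** The t-test version gives 69.9% at 80 per group. If the endpoint is instead treated as a simple proportion, 88% against 98% reproduces 80 per group one-sided and gives 70.2% power two-sided.

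**4. What 80% two-sided power would take.** The ratio of sample sizes is (1.960 + 0.842)² / (1.645 + 0.842)² = 1.27. That gives 80 × 1.27, or 102 evaluable per group, and 102 / 0.80 = 127.5, so 128 recruited per group, against 80 and 100 in the plan.

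**5. Results that the two rules would judge differently.** At 80 per group, and if the observed spread matches the planned one, success needs an observed difference of 10 × 1.645 / 2.486 = 6.6 points under the one-sided rule and 10 × 1.960 / 2.486 = 7.9 points under the two-sided rule. A result between 6.6 and 7.9 points passes one and fails the other.

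**6. If the final test is one-sided at 0.05.** Power stays at 80%. The risk of falsely declaring superiority is 5%, against 2.5% for a two-sided 95% CI lying wholly on the favourable side.

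**7. If 80 was not sized exactly as written.** Had it been computed two-sided, the implied SD would be 10 × √40 / (1.960 + 0.842) = 22.6 points and two-sided power would be 80%; the error would then be the wording of the level. Had it been rounded up from 78 (SD 25), two-sided power at 80 would be about 72%.

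**The case against.** The strongest reply is that the protocol never commits to a two-sided test. The only sidedness it states is "the one-sided significance level at 0.05", and the p < 0.05 rule uses the same number, so the two can be read together as one consistent one-sided test. The interval is given only as "the confidence interval (CI) at 95" per cent, and a one-sided 95% confidence bound matches a one-sided 5% test exactly. The article is also directional elsewhere: Trial design calls this a superiority trial about lowering blood glucose, and the Introduction and Discussion speak of reducing it. One-sided sizing suits that aim, and a 5% one-sided level departs from convention without being an arithmetic mistake.

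Much of this stands. A reader might infer that the true power simply is 70%, or that the Sample size sentence flatly contradicts itself. The documents support neither. The 70% holds only if the final test is two-sided and 80 was sized one-sided, as stated. The sentence can be reconciled if the interval is a one-sided bound. A reader might also take 25.4 points as the sponsor's planning SD; it is only back-solved. A condensed article may leave the SD to the full protocol, so its absence is not counted as a fault here.

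The figures also describe a between-group comparison, whereas the statistical methods section names a paired-samples t-test. That is a separate matter and does not settle the sidedness of a between-group claim.

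What the reply does not remove is the mismatch. A one-sided bound is nowhere mentioned, and the stated primary hypothesis has no direction. Each way of reconciling the sections requires a change or an addition to at least one of them.

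**Conclusion.** The point holds in conditional form. As written, the level used for sizing does not fit the primary hypothesis, the decision rule and the confidence level on their ordinary reading, and the protocol does not say which governs the primary claim.

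- **Two-sided final test:** power is about 70% at 80 evaluable per group and about 79% if all 100 are evaluable, instead of 80%. This assumes that 80 was sized for exactly 80% power at one-sided 0.05 and that the groups are compared by a two-sample test. It does not depend on the SD.
- **One-sided final test at 0.05:** the stated 80% power stands, but the false-superiority risk is 5% rather than 2.5%, and neither the hypothesis nor the analysis section discloses it.

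The defect is an inconsistency in the success threshold. No calculation in the text has been shown to be wrong.

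**What to change.** State one sidedness in Objectives, Sample size and Statistical methods. The preferable choice is a two-sided 0.05 test with a two-sided 95% CI for the between-group difference, which fits the hypothesis and decision rule as they now read. Then restate the power in Sample size as about 70% at 80 evaluable per group and about 79% at 100, together with the SD or control rate that the sponsor actually used. If that assumption shows that 80 was computed two-sided, correct the word one-sided instead and keep the 80%.

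If the sponsor does intend a one-sided 5% test, the hypothesis should be made directional, the interval described as a one-sided 95% bound, and the 5% false-superiority risk stated openly.

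None of this requires extra recruitment. The cost is wording and, under the preferred choice, a less favourable stated power. Keeping 80% power at two-sided 0.05 would take 102 evaluable and 128 recruited per group; that is an option for the sponsor, and the correction does not depend on it.
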